#### Availability of Participants

We will recruit and randomize a total of 290 participants (145 randomized to the **MI**^**2 **^arm and 145 randomized to the **C **arm). Participants will be recruited from annually scheduled and well attended community events in and around the Mayetta and Garden City, KS communities. Garden City is the Finney County seat. Approximately 50% of the county population, and Garden City's population, is non-Hispanic White while 45% of the nearly 41,000 people living in Finney County are Latino (approximately 9,000 Hispanic/Latina females). Our American Indian recruitment in Northeast Kansas will include a five county region; Brown (pop. 10,009/52% female/9% AI/AN); Jackson (pop. 13,240/50% female/7% AI/AN); Doniphan (pop. 7,753/51% female/2% AI/AN); Jefferson (pop. 18,421/50% female/1% AI/AN); and Pottawatomie (pop. 19,695/50% female/1% AI/AN). The AI/AN female population in each county is: Brown = 470; Jackson = 452; Jefferson = 100; Potawatomie = 69; and Doniphan = 58.

Annual community events are common within both target communities. Amongst other events, Mayetta and surrounding areas are home to the Prairie Band Potawatomi Pow Wow (held in June) and Prairie Band Potawatomi Health Fair (September), Kickapoo Pow Wow (July), Sac and Fox Health Fair (September), and the Ioway Health Fair (October). Garden City and its surrounding communities is home to a Cinco de Mayo celebration (May), Community Mexican Fiesta (September), Tyson Health Fair (October), Binational Health Fair (October), and several community events sponsored by the six area churches. Using three CHWs per community, we anticipate being able to recruit approximately 150 women in each community. If, upon a midcourse evaluation, we determine that recruitment is behind schedule, we will supplement our recruitment efforts by partnering directly with health clinics in our target communities to recruit within clinic waiting rooms.

#### CHW/Participant Partnership Implementation Intentions (MI^**2**^) Intervention

Each participant in the **MI**^**2 **^intervention arm will receive brief one-on-one breast cancer screening education delivered in person by a CHW. Following the education information delivery, the CHW will guide participants through the Healthy Living Kansas-Breast Health computerized screening and intervention program. This program will guide participants through a screening/eligibility assessment and implementation intentions protocol via automated computerized algorithms. If, upon screening, a person is deemed eligible to participate in the randomized trial (e.g., they are eligible for but not up to date on breast cancer screening), the computer program will automatically and immediately assign them to either the intervention or control arm. The total time required per participant to complete the education session and HLK-BH notebook computer program will be kept to a maximum of 20 minutes.

For persons who are randomized to the **MI**^**2 **^intervention arm, the HLK-BH program will guide participants through a series of implementation intentions questions to fully delineate step-by-step breast cancer screening intentions of participants (the when, where and how of screening) and encourage follow through on these intentions. Breast cancer screening information, relevant to the stated intentions of the participant will then be delivered over the remaining course of the program. Implementation intentions questions and breast cancer screening information in the HLK-BH program will be adapted with input from community and advisory board members and from questions and materials used successfully in our prior implementation intentions-based cancer screening studies. The HLK-BH program will, by necessity, consist of two primary phases designed to: 1) elicit participants' implementation intentions and 2) encourage follow through. Although implementation intention tasks will differ for each participant, a sample list of tasks is presented in Table 3. In a typical program session, participants will be asked to declare whether they "intend" to get breast cancer screening. If they are unsure or do not intend to get screened within the next 120 days, they will be taken through a series of implementation intention questions that specifically address when, where, and how they will gather more information on breast cancer screening or engage in discussions about breast cancer screening with their physician, family, or peer group. Individuals intending to receive screening will be led through a series of questions about when, where, and how they will be screened. The questions will include specifics on making contacts with the health care system, obtaining authorizations from health care providers, scheduling appointments, arranging for transportation to mammography locations, and avoiding potential behavioral pitfalls along each juncture of the aforementioned process. All implementation intention questions will be tailored to the race/ethnicity of the participant. The HLK-BH program also will provide suggestions that might help the participant overcome obstacles to test completion (inconvenience, pain, embarrassment). To assist persons with low literacy levels, the computer program will evaluate and organize data as they are entered and then deliver a tailored intervention message using video clips and narrated graphics. In this manner, the program will select messages that are tailored to race/ethnicity and gender matched to individual participants. Participants will wear headphones. The primary goal of the HLK-BH program for **MI**^**2 **^participants is to clarify implementation intentions and address barriers which might prevent follow through on these intentions.

**Table 3 T3:** Sample Implementation Intention Task Analyses for MI^2 ^Participants

Participants "Unaware" Stage for Breast Cancer Screening	Participants "Decided/Deciding" About Breast Cancer Screening
• Identify a source for more breast cancer information • Specify a goal date by which the breast cancer information source will be contacted • Identify steps necessary to contact the breast cancer information source (e.g., if breast cancer information source is a health care provider: obtain telephone number, schedule an appointment, arrange transportation to and from the appointment if necessary) • Identify breast cancer screening questions to ask • Describe how information gathered will be saved and additional contacts who may be used as "second opinions"	• Identify health professional that will supply mammography referral, if necessary • Declare how to request a referral • Assess insurance status • Identify eligibility for Early Detection Works program • Telephone to schedule exam (e.g., who to call, number to call, information to have available to schedule exam) • Identify exam preparation tips to increase comfort • Arrange transportation to and from appointment if necessary • Arrange for child care if necessary

Immediately following completion of the HLK-BH session, participants will receive a printed "Implementation Intentions Confirmation Contract" that will serve as a final indicator of the stated and agreed to plan that the HLK-BH session produced. This contract will serve as a written reminder and reinforcement for each participant's breast cancer screening implementation intentions and will be tailored to each individual's Precaution Adoption Process Model behavioral stage of readiness. As with the notebook computer screens, the KU Design for Health unit will work with us to ensure the delivery of high quality, highly readable and usable printed contract.

#### Control Arm (**C**) Intervention

Each participant in the **C **intervention arm will receive the same brief one-on-one breast cancer screening education information delivered in person by a CHW as **MI**^**2 **^participants. Following the education information delivery, the CHW will guide participants through the Healthy Living Kansas-Breast Health computerized screening and intervention program. This computerized program will guide participants through a screening/eligibility assessment and additional breast health and screening education protocol. If, upon screening, a person is deemed eligible to participate in the randomized trial (e.g., they are eligible for but not up to date on breast cancer screening), the computer program will automatically and immediately assign them to either the intervention or control arm. The **C **intervention will also be infused with audio-narratives delivered by a non-matched clinician reader. This clinician will read textual material comparable to that provided in educational pamphlets distributed by the NCI and Centers for Disease Control. The information will cover prevalence and distribution of breast cancer, rates of mortality, the potential mortality reduction with early detection, early signs and symptoms of breast cancer, and primary preventive measures for reducing the incidence of breast cancer. A small amount of supplemental material may be provided to assure that the length of this session matches the length of the multimedia session provided to **MI**^**2 **^participants. As with **MI**^**2 **^participants, the total time required per participant to complete the education session and HLK-BH computer program will be kept to a maximum of 20 minutes.

During the control arm HLK-BH program, participants will be reminded of the importance of breast cancer screening and highlight NCI-recommended healthy breast behaviors such as regular physical activity and a diet rich in fruits and vegetables. These HLK-BH sessions will rely on a "health educator" methodology. Furthermore, the CHW will be instructed to not initiate specific behavioral advice or use behavioral counseling strategies following participant completion of the control arm HLK-BH program. If, however, a participant asks for specific behavioral advice related to the formulation of implementation intentions, the CHWs will answer the participant's question briefly and document the question and their reply.

All participants (intervention and control) will received a $25 gift card to reimburse them for their time involved with completing the HLK-BH program assessment.

#### 120-Day Post Randomization Follow-Up

All **MI**^**2 **^and **C **participants will receive a follow-up telephone call from a CHW to reassess breast cancer screening status. For example, participants will be asked if screening was performed within the last 120 days since the initial intervention, and if so, when it was performed, and when the participant plans to have their next routine breast cancer screening examination. The CHW also will re-administer portions of the HLK-BH program questions via the telephone and ask questions regarding breast cancer testing utilization, breast cancer screening barriers, perceived breast cancer susceptibility, screening self-efficacy, and breast cancer risk status and reassess Precaution Adoption Process Model behavioral breast cancer screening stage. Program evaluation and satisfaction questions will also be asked of each participant near the end of this final assessment. By re-administering portions of the HLK-BH program questions at the 120-day post randomization follow-up, the research team will be able to evaluate the differential impact of the **MI**^**2 **^intervention compared to the **C **intervention on the primary (e.g., breast cancer screening utilization) and secondary outcomes (e.g., breast cancer screening barriers and progression through the PAPM stages). Refer to Figure 2 for an overview of the flow of research participants.

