**Methods/Design:**

In the proposed program, community health workers will meet with rural-dwelling Latina and American Indian women one-on-one to educate them about breast cancer and screening and guide them through a computerized and culturally tailored "implementation intentions" program, called *Healthy Living Kansas - Breast Health*, to promote breast cancer screening utilization. We will target Latina and AI/AN women from two distinct rural Kansas communities. Women attending community events will be invited by CHWs to participate and be randomized to either a mammography "implementation intentions" (**MI**^**2**^) intervention or a comparison general breast cancer prevention informational intervention (**C**). CHWs will be armed with notebook computers loaded with our Healthy Living Kansas - Breast Health program and guide their peers through the program. Women in the **MI**^**2 **^condition will receive assistance with operationalizing their screening intentions and identifying and addressing their stated screening barriers with the goal of guiding them toward accessing screening services near their community. Outcomes will be evaluated at 120-days post randomization via self-report and will include mammography utilization status, barriers, and movement along a behavioral stages of readiness to screen model.

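### The unverified, self-reported primary outcome is collected by the CHW team that delivers both arms, with no stated masking of the caller; reallocating the calls would reduce caller-side bias at little cost

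*Protocol article*

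**What the plan says.** - **Outcome source.** Protocol article, Abstract, Methods/Design: "Outcomes will be evaluated at 120-days post randomization via self-report and will include mammography utilization status".
- **Who asks.** 120-Day Post Randomization Follow-Up: in both arms, "participants will receive a follow-up telephone call from a CHW to reassess breast cancer screening status". The woman is asked whether she was screened and, if so, when. Of the later items the section says: "Program evaluation and satisfaction questions will also be asked of each participant near the end of this final assessment".
- **Who delivers.** In the MI2 section, "the CHW will guide participants through the Healthy Living Kansas-Breast Health computerized screening and intervention program", after giving brief education in person. The Control Arm section describes the same CHW role.
- **Who knows the arm.** Control Arm section: "the CHW will be instructed to not initiate specific behavioral advice or use behavioral counseling strategies following participant completion of the control arm". The CHW must also document her replies if a control woman asks about implementation intentions. Neither is possible without knowing the arm. MI2 women also leave with a printed plan: "This contract will serve as a written reminder and reinforcement for each participant's breast cancer screening implementation intentions".
- **Team size.** Availability of Participants: "Using three CHWs per community, we anticipate being able to recruit approximately 150 women in each community".
- **Analysis.** Data Analysis, Aim #1 plans a χ² test on a 2 × 2 table. Logistic regression follows if demographics are seriously imbalanced. The sensitivity analysis concerns women whose outcome is missing.

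The follow-up section does not say which CHW calls which woman or whether the caller can see the arm. It mentions no check of reported mammograms against records.

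**The concern.** Over-reporting that is equal in both arms mainly dilutes the difference. Over-reporting that is greater in MI2 produces a difference where none exists, in the direction of the hypothesis.

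Two routes could make it unequal:

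- **Caller side.** A CHW who knows the arm, or who helped make the plan, may probe differently or record an ambiguous answer differently.
- **Participant side.** An MI2 woman who agreed a plan may be reluctant to say that it was not kept, more so to the peer who helped her make it. Control women made no such plan.

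The planned analyses would not show either. Adjusting for demographics does not correct a misclassified outcome, and the sensitivity analysis varies only the unknown outcomes, not the reported ones.

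**Working it through.** **Inputs from Sample Size and Sample Size Justification:** 30% screened in MI2 and 15% in control; two-sided α = 0.05; 121 per arm for 80% power; 290 randomized; up to 20% attrition.

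**Step 1: reproduce the plan's figure.** With the pooled-variance formula and no continuity correction, mean rate (0.30 + 0.15)/2 = 0.225:

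n = [1.960·√(2 × 0.225 × 0.775) + 0.842·√(0.30 × 0.70 + 0.15 × 0.85)]² / 0.15² = 120.5, rounded up to 121 per arm.

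Power at 121 per arm is 80.2%. The plan's figure reproduces.

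**Step 2: evaluable number.** 290 × 0.80 = 232, or 116 per arm.

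**Step 3: bias model.** Let the true rate be 15% in both arms, so that there is no effect. Let *d* be the excess share of unscreened MI2 women who report a mammogram, with no over-reporting in control. Then

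observed MI2 rate = 0.15 + 0.85·*d*, and spurious difference = 0.85·*d*.

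The documents give no value for *d*; the values below are assumptions. The type I error is the probability that the uncorrected two-sided 5% χ² test rejects, summed exactly over the two binomial distributions at 116 per arm.

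| Assumed *d* | Spurious difference (points) | Type I error |
|---|---|---|
| 0% | 0 | 5.0% |
| 1% | 0.85 | 5.4% |
| 2% | 1.7 | 6.5% |
| 3% | 2.55 | 8.2% |
| 5% | 4.25 | 13.8% |
| 8% | 6.8 | 26.8% |
| 10% | 8.5 | 37.8% |

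At *d* = 5% the spurious difference is 4.25/15 = 28% of the planned 15-point effect. At 121 per arm the last three error rates would be 14.4%, 28.1% and 39.5%, so the choice of evaluable number matters little.

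**Step 4: equal over-reporting.** If 5% of unscreened women in each arm over-report, a true 30% versus 15% is observed as 0.30 + 0.70 × 0.05 = 33.5% versus 0.15 + 0.85 × 0.05 = 19.25%. Type I error stays at about 5%, and power at 116 per arm falls from about 79% to about 70%.

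**Step 5: is there someone else to call?** With three CHWs per community, two need not have run a given woman's session. The reallocation therefore needs no new staff.

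**The case against.** The case against has five parts.

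- **Same caller.** A reader might infer that the CHW who ran the session also makes the call. The text says only that a CHW calls. It allows the session CHW but does not require her, and an article may leave call assignment to a fuller protocol. This stands as a limit. The point is that the design as stated assigns the call to the delivering team without a safeguard.
- **Commitment.** A reader might infer that every MI2 woman committed to a mammogram date. The MI2 section says that women who are unsure or not intending plan information-seeking only, and the Implementation Intentions section says that an intending woman may be asked for a date. The pressure applies to part of the arm.
- **Question order.** It is tempting to put the mammogram question first, before the barriers and Precaution Adoption Process Model (PAPM) items. The documents do not support this. The PAPM Stage section requires staging before the behaviour questions, to protect what is the Aim #3 outcome. Project Instrumentation gives all measures except implementation intentions to both arms, so barriers and PAPM items need not reveal the arm. The program and satisfaction items already come near the end.
- **Reach of the remedy.** Changing the caller does not blind the woman, who knows what she received and holds a printed contract. The Community Health Workers section describes weekly group calls, which may weaken masking in a team of three. Both limits stand.
- **Size.** Both arms get the same CHW education, the gift card and a CHW call, and control women are also reminded that screening matters. Much over-reporting may be shared, and an excess of 1% to 3% leaves the error near nominal. This is fair, and is why the full range is shown.

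**Conclusion.** The concern holds as a correctable weakness in outcome collection. An unverified self-report is taken by a team that delivers both arms and learns the allocation; no masking is stated, and no planned analysis addresses false reports.

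The size depends on an assumption. It runs from negligible (5.4% at a 1% excess) to serious (37.8% at a 10% excess), given a true rate of 15% in both arms, no over-reporting in control and 116 evaluable women per arm. The direction, toward MI2, is plausible but also assumed.

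A reader might conclude that the trial's result will be biased, or that reallocating the calls would solve the problem. The documents support neither. They show that the bias is possible and that one of its two routes can be narrowed cheaply; how much the change would achieve cannot be derived from them.

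**What to change.** In 120-Day Post Randomization Follow-Up, specify that:

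1. each call goes to a CHW in the same community who did not run that woman's session;
2. the call list does not show the arm;
3. the call follows a fixed script that asks the date and facility of any reported mammogram;
4. PAPM staging stays before the screening-behaviour questions, as the PAPM Stage section requires, and program and satisfaction items stay last;
5. the caller records whether she learned or guessed the arm.

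The cost is call scheduling and script preparation; staff and sample size do not change. Losing the familiar caller may slightly lower response. The report should also state that women were aware of what they received and that the outcome was self-reported, because these steps leave participant-side over-reporting in place.

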**Figure 2 F2:**
[figure not shown]
**Flow of Participants**.

#### Project Instrumentation

The purpose of all survey project instrumentation is to collect data for use in developing individually tailored materials and to allow for analysis of study main effects with appropriate covariate controls. The measured constructs should also provide information on which variables are responsible for intervention effects. All measures except for "Implementation Intentions" measures will be given to study participants prior to randomization and thus to participants in both arms (**MI**^**2 **^and **C**).

Though many of the scales and instruments selected for the study have been used in previous studies, the complete baseline survey instrument will be pilot tested with Latina and female AI/AN community members within our two target communities. Feedback from this pilot testing phase will be used to revise the instrument and to prepare it for administration. Our goal is to establish an instrument that can be completed in 10-15 minutes using a notebook computer.

#### Demographics

Data on gender, education, marital status, age, income, employment status, and race/ethnicity will be collected. With respect to race/ethnicity, study participants will be asked to identify themselves as being Black/African American (and allow for further ethnic identification as U.S. born, Caribbean immigrant, African immigrant, Jamaican, etc.), Hispanic, White, Native American/American Indian, Asian, or Other [53].

#### PAPM Stage

The model's authors provide a staging algorithm and recommended question formats for staging other health behaviors [40,54]. We will adapt the staging questions to breast cancer screening and use a six-item scale: "Have you ever heard about breast cancer screening?"; "Have you been tested for breast cancer?" and "Which of the following best describes your thoughts about getting tested for breast cancer: I've never thought about it, I'm undecided, I've decided I don't want to, I've decided I want to get tested." Necessarily, stage will be asked prior to the behavior questions so that responses are not influenced or triggered by the questions about specific screening tests.

#### Perceived Susceptibility to Breast Cancer, Perceived Screening Benefit, and Screening Barriers

We will utilize the Revised Susceptibility, Benefits, and Barriers Scale developed by Champion [55]. This 19 item scale has been used widely by researchers and has shown to be a reliable and valid assessment.

